# Summary

**Introduction**

Staging is important for determining the appropriate treatment and for estimating the prognosis in patients with ovarian cancer. It is therefore relevant to detect occult metastasis in the peritoneum, omentum, and retroperitoneal nodes. In case of low stage ovarian cancer (I t / m IIa) patients are eligible for surgical treatment. If low-stage ovarian cancer is confirmed by histological examination, chemotherapy can be omitted.

In case of high stage ovarian cancer (IIb t / m IV) primary debulking is standardly followed by chemotherapy. In case of high stage ovarian cancer, the aim is to remove all macroscopic metastases. And, if this not possible, to strive for debulking to <1 cm residual tumor diameter.

For low stage ovarian cancer, it is important to perform an accurate staging procedure to detect all microscopic metastases, as this is of importance for the prognosis and further treatment. Hence a surgical staging procedure is performed. (www.oncoline.nl/epitheliaal-ovariumcarcinoom)

Recent preclinical studies have shown that it is possible to detect peritoneal ovarian cancer metastases using near-infrared (NIR) fluorescence imaging with indocyanine green (ICG). If these results can be translated to the clinic, this could possibly lead to better identification of occult peritoneal, omental and retroperitoneal metastases, and consequently to better staging.

**Research Question**

Is it possible to identify occult peritoneal, omental and retroperitoneal ovarian cancer metastases by NIR fluorescence imaging using indocyanine green?

**Population**

In order to verify the sensitivity of the technique in detecting omental and peritoneal metastases patients with stage IIb to IIIc ovarian cancer planned for a debulking procedure will be enrolled in this pilot study. In addition, patients with stage I or IIa ovarian cancer planned for a surgical staging procedure will be enrolled.

**Trial design**

Patients will be divided into two groups. One group with low stage ovarian cancer, and one group with high stage ovarian cancer. All patients in both groups will be administered ICG during at start of the surgery.

During surgery imaging with a NIR fluorescence camera system will be performed at different time points. After resection, NIR fluorescence imaging of the resected tissue will be performed at the pathology department.

**End points**

The primary endpoint is the percentage of peritoneal, omental or retroperitoneal ovarian cancer metastases identified with NIR fluorescence imaging (defined as the part of the pathology proven ovarian cancer metastases that also show NIR fluorescence)

# Introduction

Ovarian cancer is the 6th most common cancer among women. Worldwide every year 200,000 women are diagnosed with ovarian cancer. The prognosis of these patients is primarily dependent on the stage (FIGO staging) of the tumor, and of the accuracy of the surgical treatment. Patients with low stage ovarian cancer (FIGO I-IIa) have a 5-year survival of 75% -100%. The 5-year survival of patients with high stage ovarian cancer (FIGO IIb-IV) is 20% -60%. ([www.oncoline.nl/epitheliaal-ovariumcarcinoom](http://www.oncoline.nl/epitheliaal-ovariumcarcinoom))

Surgical resection and chemotherapy are the cornerstones of the treatment of ovarian cancer. For low stage ovarian cancer surgical resection of the uterus, adnexa and omentum is sufficient in most cases, provided that the surgical staging is optimally performed. In the Netherlands, no consensus exists on whether to give chemotherapy in case of low stage ovarian cancer with a grade III tumor. When staging is incomplete and restaging is not possible, low stage ovarian cancer is treated like high stage ovarian cancer with surgery followed by chemotherapy, due to the significant risk of micro metastases. (www.oncoline.nl/epitheliaal-ovariumcarcinoom)

However, about 70% of women present with advanced stage ovarian cancer (FIGO IIb-IV). The amount of tumor remaining after debulking is the most important prognostic factors in this group of patients and therefore the goal of surgery is to completely resect all tumor. After resection, these patients receive chemotherapy.(1)

In surgical debulking the aim is to leave no macroscopic residual tumor, and when this is not possible, to only leave residual tumor <1 cm in diameter. Complete surgical debulking is achieved when no tumor is visible after resection. After a complete debulking surgery, the survival rate is significantly better in comparison to optimal (<1 cm residual tumor), or sub-optimal (> 1 cm residual tumor) debulking surgery.(2)

With modern imaging techniques, such as CT and MRI, preoperative localization and staging of tumors can be done reasonably well. However, preoperative imaging and gynecological examination alone are not sufficient in estimating whether a complete or optimal debulking can be carried out. Therefor in the Netherlands, it is currently investigated whether a preoperative laparoscopy can contribute to a better distinction between patients eligible for primary debulking and patients eligible for neo-adjuvant chemotherapy followed by interval debulking in advanced ovarian cancer.(3)

In patients with low stage ovarian cancer, detecting occult metastases has major implications for the treatment, as treatment of patients with metastasised disease involves chemotherapy after the surgical resection.(4)

In order to detect these metastases a staging surgery is performed. This involves taking biopsies of any adhesions surrounding the (area of the) primary tumour, all macroscopic suspect areas, blind biopsies of amongst others the peritoneum, and lymph node sampling. (www.oncoline.nl/epitheliaal-ovariumcarcinoom)

A recent development is the use of fluorescence imaging to visualize also tumors during surgery. This technique makes use of special fluorescent dyes, in combination with NIR light. This NIR light is not visible to the human eye, but can be detected with a camera system. The advantages of this technique are that it does not involve the use of harmful radiation, yet has a penetration depth of approximately 1 cm in tissue. One of the fluorescent dyes which is currently approved for clinical use is ICG. ICG is considered safe for use in humans and has been clinically used since the nineteen fifties for liver function tests and retinal angiography. Moreover, ICG has already been used in image-guided surgery research into detection of the sentinel node in breast, vulva and liver tumors with NIR fluorescence.(5)

Because in vivo ICG binds to serum proteins, it behaves as a macromolecule in the circulation. It is known that macromolecules accumulate in tumor tissue due to increased vascular permeability and reduced drainage in these tissues. This is known as the "enhanced permeability and retention" (EPR) effect.(6;7) In previous clinical trials in breast and gastric cancer patients it was possible to distinguish tumor tissue from the surrounding tissue using ICG in combination with optical imaging.(8-13)

A recent study of Kosaka et al.(14) has shown that in an animal model it is possible to detect peritoneal metastases of ovarian cancer with NIR fluorescent imaging after an intravenous injection of 3.5 mg / kg of ICG. Based on the above mentioned data, it may also be possible to identify peritoneal, omental or retroperitoneal metastases in ovarian cancer patients with NIR fluorescent imaging after intravenous administration of ICG.

In addition, Ishizawa et al. demonstrated successful visualization of hepatocellular carcinoma using NIR fluorescent imaging and intravenous injection of 0.5 mg/kg ICG during a laparoscopic hepatectomy.(15)

## Clinical Problem

Despite recent advancements in preoperative imaging, it remains challenging to detect peritoneal, omental and retroperitoneal metastases during staging surgery for early stage ovarian cancer. Undetected metastasized disease could lead to inadequate treatment of patients, due to the unjustified of chemotherapy.

Adequate imaging and real-time detection of these metastases could possibly improve the surgical staging procedure, consequently permitting a better selection of patients that should receive additional chemotherapy.

## Hypothesis / aim

Preclinical studies have shown that ICG can be used for the identification of peritoneal ovarian carcinoma metastases. Therefor we have the hypothesis that in after intravenous injection of ICG it is possible to intraoperatively detect ovarian cancer metastases using NIR fluorescent imaging.

Research Question:

Is it possible to identify peritoneal, omental or retroperitoneal ovarian cancer metastases in clinical low stage ovarian cancer patients using NIR fluorescence imaging and ICG?

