## Population

In this study, patients with stage IIb t / m IIIc ovarian cancer who are eligible for primary debulking surgery will be enrolled to study feasibility of detection of metastases. In addition, patients with early stage I-IIa ovarian cancer will be enrolled to investigate if identification of occult metastases is possible within this patient population.

.

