### Inclusion criteria

- Patients with suspected stage IIb t / m IIIc ovarian cancer who are eligible for primary debulikng surgery
- Patients with suspected stage I or IIa eligible for a surgical staging procedure.
- Age over 18 years.

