## Study design

All patients diagnosed with stage IIb t / m IIIc ovarian cancer eligible for debulking surgery will be included. In addition, all patients diagnosed with stage I or IIa ovarian cancer eligble for a surgical staging procedure will be enrolled.

All patients (n = 15) will be administered ICG (20 mg) during the surgery. Intraoperative NIR fluorescence imaging findings will be compared with clinical findings by the gynecologist during the surgery.

During the surgery, standard procedure will be followed and biopsies of clinically suspected areas will be obtained. Additional NIR fluorescent spots, that were not detected by the gynaecologist with usual visual/tactile methods, will also be removed and sent to the pathology department for histopathological assessment. Immediately after the resection, the resected tissue specimens will be transported to the pathology department of the LUMC, where specimens will be photographed and additional NIR fluorescent imaging will be performed. Hereafter the department of pathology’s standard procedure for assessing the resected specimens will be followed for both specimens detected under usual methods and specimens detected under NIR fluorescence imaging.

When it is decided by the attending gynaecologist to also perform a laparoscopic staging (whether or not in the context of the LAPOVCA study), a laparoscopic intra-operative NIR fluorescence imaging system can be used. (See umbrella protocol P10.001 protocol, version 3.0, Appendix 4 and 5 for a detailed description of the laparoscopic camera system).

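### The primary endpoint pools metastases from both stage groups, evident and occult, while the research questions concern low-stage patients (section 2.2) or occult lesions (Summary)

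*Protocol*

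**What the plan says.** The protocol states its question in two ways. Section 2.2 (Hypothesis / aim) limits it by patient: "ovarian cancer metastases in clinical low stage ovarian cancer patients using NIR fluorescence imaging and ICG". The Summary limits it by lesion and names no stage: "Is it possible to identify occult peritoneal, omental and retroperitoneal ovarian cancer metastases by NIR fluorescence imaging using indocyanine green".

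The clinical need is placed in early disease. Section 2.1 says "it remains challenging to detect peritoneal, omental and retroperitoneal metastases during staging surgery for early stage ovarian cancer". Section 2.3 (Population) gives each group its own role. The high-stage group serves to show whether detecting metastases is feasible. For the low-stage group: "patients with early stage I-IIa ovarian cancer will be enrolled to investigate if identification of occult metastases is possible within this patient population".

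The primary endpoint (Summary and section 2.7) is the percentage of pathology-proven peritoneal, omental or retroperitoneal metastases that fluoresce. It is not restricted to, or split by, stage group or type of lesion. A secondary endpoint counts additional metastases found by fluorescence. Section 2.3.3 sets 15 patients in total, and neither it nor section 2.4 divides them between the groups.

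**The concern.** The Summary's trial design creates two groups, but no endpoint uses the division. The groups also feed the primary denominator very unequally. A high-stage patient comes to debulking with spread already suspected. A low-stage patient comes to staging with none suspected and adds a lesion only if an unsuspected metastasis is proven. The pooled percentage is therefore likely to be driven by the group that was enrolled to show feasibility. It could read high even if the technique failed on every lesion in the patients named in section 2.2. A reader who sets the result beside that question could take it as evidence about low-stage patients when it contains almost none.

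**Working it through.** There is no planned figure to reproduce, because section 2.3.3 says that no formal sample size calculation was done.

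**Inputs.** The total of 15 patients is from section 2.3.3. Everything else is assumed, because the protocol does not give it:
- n_L and n_H, the low-stage and high-stage patients: 5 and 10, then other splits;
- q, the proportion of low-stage patients with a proven metastasis: 10%, 20% or 30%;
- m_L, the lesions per positive low-stage patient: 1 or 2;
- m_H, the lesions per high-stage patient: 1 to 10.

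**Low-stage share of the denominator (expected counts)** = n_L·q·m_L / (n_L·q·m_L + n_H·m_H).

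| n_L / n_H | q | m_L | m_H | Low-stage share |
|---|---|---|---|---|
| 5 / 10 | 0.1 | 1 | 10 | 0.5/100.5 = 0.5% |
| 5 / 10 | 0.1 | 1 | 3 | 0.5/30.5 = 1.6% |
| 5 / 10 | 0.3 | 1 | 3 | 1.5/31.5 = 4.8% |
| 5 / 10 | 0.3 | 2 | 3 | 3/33 = 9.1% |
| 5 / 10 | 0.3 | 2 | 1 | 3/13 = 23.1% |
| 10 / 5 | 0.3 | 2 | 3 | 6/21 = 28.6% |
| 12 / 3 | 0.3 | 2 | 1 | 7.2/10.2 = 70.6% |

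With 5 and 10 patients and 3 to 10 lesions per high-stage patient, high-stage lesions make up 90.9% to 99.5% of the endpoint.

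To see what reverses this, take q = 0.3 and m_L = 2. Low-stage lesions are then the majority only if m_H is below 6/5 = 1.2 with 10 low-stage patients, or below 7.2/3 = 2.4 with 12. It takes a mostly low-stage sample and very few lesions per high-stage patient.

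**Chance that no low-stage patient has a metastasis** = (1 − q)^n_L. With n_L = 5:
- q = 10%: 0.9^5 = 59%;
- q = 20%: 0.8^5 = 33%;
- q = 30%: 0.7^5 = 17%.

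The expected number of positive low-stage patients is 5q = 0.5 to 1.5. If one lesion is proven and it fluoresces, the exact 95% interval is 2.5-100%; for two of two it is 15.8-100%.

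**Dilution.** Suppose 95% of lesions are high-stage with 90% of them fluorescent, and none of the 5% low-stage lesions fluoresce. The pooled endpoint is 0.95 × 0.90 + 0.05 × 0 = 85.5%.

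**The secondary count.** An additional lesion found because it fluoresces is fluorescent by definition. The count shows that some occult lesions were found, but not what share of them.

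**The case against.** Much of the protocol fits the pooled endpoint. The hypothesis sentence in section 2.2 has no stage limit, the primary objective in section 2.6 speaks of ovarian cancer patients generally, and section 2.3.3 promises an estimate of feasibility. High-stage patients are enrolled on purpose and for a stated reason. The search for further lesions has its own secondary objective and endpoint, and section 2.4 already separates what the gynaecologist found from additional fluorescent spots. This is a declared pilot, and tables by group may be left to an analysis plan that is not shown. All of this stands. It makes the matter one of alignment and limits on the claim, not of a broken design. It does not remove the mismatch: which patients and lesions the primary question concerns is for the protocol to settle, and its two questions and its endpoint differ.

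Stronger readings are tempting, and the text does not carry them.
- A reader might infer from the Introduction's "about 70% of women present with advanced stage ovarian cancer (FIGO IIb-IV") that most of the 15 will be advanced. That figure describes all women at presentation and includes stage IV. Eligibility is IIb to IIIc with primary debulking, so the share here is unknown.
- A reader might infer that visible deposits are certain to supply nearly the whole answer. No lesion counts are given, and high-stage patients may have occult lesions too.
- Section 2.3.1 has "Patients with suspected stage I or IIa eligible for a surgical staging procedure", while section 2.4 has "all patients diagnosed with stage I or IIa ovarian cancer eligble for a surgical staging procedure will be enrolled". A reader might infer that final pathology would move positive patients out of the low-stage group. Nothing says that final stage is used. The groups are tied to the planned operation, and section 2.2 speaks of clinical stage, so pre-operative stage is the natural reading.
- A reader might hold that detection of evident lesions cannot carry over to occult ones. The protocol offers no evidence either way.

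**Conclusion.** The point holds as a mismatch between question and endpoint that can be read directly in the text. Its size is conditional. In the 5 and 10 split, with 10-30% of low-stage patients positive and at least 3 lesions per high-stage patient, roughly nine-tenths or more of the lesions are high-stage, and there is a substantial chance that the low-stage group contributes nothing. The direction survives most plausible mixes, but not all. The documents do not show that the sponsor will present the pooled figure as a low-stage result; they leave that reading open. The point is worth settling before results are reported, because it decides what the trial can claim. It does not call the enrolment of high-stage patients or the total of 15 into question.

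**What to change.** - State one primary question in the Summary and section 2.2, consistent with sections 2.6 and 2.7: feasibility of detection, estimated in the high-stage group, which is the role that the Summary's population paragraph and section 2.3 give it.
- Report the primary percentage and the count of additional metastases separately by stage group, and by lesions found by the usual visual and tactile methods versus additional or occult lesions. The occult category should include metastases proven only at pathology, for example from blind biopsies or node sampling, whether or not they fluoresced. Otherwise its percentage is 100% by construction.
- State that the low-stage result is exploratory and supports no claim about sensitivity.
- As a minor clarification, define group membership by pre-operative suspected stage, kept whatever the final pathology, and reconcile the wording of sections 2.3.1 and 2.4.

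The cost is a wording amendment and stratified tables from data that the trial already collects, with no added patients or procedures. The price is a narrower claim for low-stage patients and some very small cells, which should be shown as counts with exact intervals.

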## Population

In this study, patients with stage IIb t / m IIIc ovarian cancer who are eligible for primary debulking surgery will be enrolled to study feasibility of detection of metastases. In addition, patients with early stage I-IIa ovarian cancer will be enrolled to investigate if identification of occult metastases is possible within this patient population.

.

### Inclusion criteria

- Patients with suspected stage IIb t / m IIIc ovarian cancer who are eligible for primary debulikng surgery
- Patients with suspected stage I or IIa eligible for a surgical staging procedure.
- Age over 18 years.

### Exclusion criteria

- Allergy or hypersensitivity to sodium iodide, iodine or ICG
- Hyperthyroidism and autonomous thyroid adenoma
- Pregnancy
- Severe renal impairment

### Sample size

In this phase 2 pilot study, the value of NIR fluorescent imaging in detection of peritoneal, omental and retroperitoneal ovarian metastases after ICG injection will be studied. Because this study was designed as a pilot study no formal sample size calculation could be performed. Based on the heterogeneity of ovarian cancer metastases in the daily clinic, we expect a total of 15 patients will need to be enrolled. With this sample size we should be able to make a reasonable estimate of the feasibility of the detection of ovarian cancer metastases with NIR fluorescence imaging and ICG. If negative results are seen in all patients, we will consider stopping the pilot study prematurely.

## Study design

All patients diagnosed with stage IIb t / m IIIc ovarian cancer eligible for debulking surgery will be included. In addition, all patients diagnosed with stage I or IIa ovarian cancer eligble for a surgical staging procedure will be enrolled.

All patients (n = 15) will be administered ICG (20 mg) during the surgery. Intraoperative NIR fluorescence imaging findings will be compared with clinical findings by the gynecologist during the surgery.

During the surgery, standard procedure will be followed and biopsies of clinically suspected areas will be obtained. Additional NIR fluorescent spots, that were not detected by the gynaecologist with usual visual/tactile methods, will also be removed and sent to the pathology department for histopathological assessment. Immediately after the resection, the resected tissue specimens will be transported to the pathology department of the LUMC, where specimens will be photographed and additional NIR fluorescent imaging will be performed. Hereafter the department of pathology’s standard procedure for assessing the resected specimens will be followed for both specimens detected under usual methods and specimens detected under NIR fluorescence imaging.

When it is decided by the attending gynaecologist to also perform a laparoscopic staging (whether or not in the context of the LAPOVCA study), a laparoscopic intra-operative NIR fluorescence imaging system can be used. (See umbrella protocol P10.001 protocol, version 3.0, Appendix 4 and 5 for a detailed description of the laparoscopic camera system).

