## End points

**Primary End Point**

The primary endpoint is the percentage of peritoneal, omental or retroperitoneal ovarian cancer metastases identified with NIR fluorescence imaging (defined as the part of the pathology proven ovarian cancer metastases that also show NIR fluorescence)

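### The primary percentage pools metastases that NIR found independently with surgeon-known lesions that also fluoresce, and NIR calls are not logged separately, so a high value would not show that NIR identifies occult disease

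*Protocol*

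**What the plan says.** The research question in the protocol Summary is: "Is it possible to identify occult peritoneal, omental and retroperitoneal ovarian cancer metastases by NIR fluorescence imaging using indocyanine green". The Summary's Population paragraph gives the high-stage group a different task: "In order to verify the sensitivity of the technique in detecting omental and peritoneal metastases patients with stage IIb to IIIc ovarian cancer" are enrolled, alongside stage I and IIa patients having a staging procedure.

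The primary endpoint (Summary and section 2.7) is a percentage of metastases identified by NIR, "defined as the part of the pathology proven ovarian cancer metastases that also show NIR fluorescence".

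Section 2.4 describes how lesions reach the pathologist. The first route is usual care: "During the surgery, standard procedure will be followed and biopsies of clinically suspected areas will be obtained". The second route exists only because of the camera and covers lesions that usual care would have left behind: "Additional NIR fluorescent spots, that were not detected by the gynaecologist with usual visual/tactile methods, will also be removed". On the relation between the two inspections it says only that "Intraoperative NIR fluorescence imaging findings will be compared with clinical findings by the gynecologist during the surgery". At the pathology department there is a further reading of the resected tissue, "where specimens will be photographed and additional NIR fluorescent imaging will be performed". The endpoint does not say whether fluorescence seen only on that later reading counts.

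The Introduction adds that staging surgery includes "blind biopsies of amongst others the peritoneum, and lymph node sampling". One secondary endpoint in section 2.7 is the number of additional metastases detected with NIR. Another is the tumour-to-background ratio.

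**The concern.** The endpoint is labelled as identification, but it requires only that a proven metastasis fluoresces. It does not require that NIR drew attention to the lesion. A camera pointed at a nodule already found by eye or hand scores the same as a call made from the NIR image alone. No order of inspection is set and no log of NIR calls is kept before the comparison, so knowledge of where the tumour lies may influence what is called fluorescent.

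Occult metastases offer no such cue and may also differ from evident ones in size and signal. These are two separate problems: cueing, and a different spectrum of lesions. Both separate the pooled percentage from the occult-disease question. A technique that lights up known tumour, but would seldom lead the surgeon to unknown tumour, could still produce a high primary result.

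This cannot be left to a later analysis plan. If the independent NIR call and the route of detection are not recorded during surgery, no analysis can recover them.

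**Working it through.** **Plan's own figure.** There is none to reproduce. Section 2.3.3 gives 15 patients without a calculation, and no expected percentage is stated.

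**Routes into the endpoint, from section 2.4 and the Introduction:**

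| Route | In denominator | In numerator |
|---|---|---|
| Clinically suspected, then biopsied or resected | yes, if malignant | if it fluoresces, cued or not |
| NIR-only spot | yes, if malignant | always, by construction |
| Blind biopsy or node sampling | yes, if malignant | only if it fluoresces |
| Missed by both and not sampled | no | no |

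The endpoint is therefore a mixture. The question is how far the mixture can depart from the rate at which NIR finds occult lesions.

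**Inputs (all assumed; the protocol gives none):**
- u: share of all metastases that are occult
- sc: share of surgeon-known metastases called fluorescent
- su: share of occult metastases that NIR finds without a cue
- b: share of NIR-missed occult metastases still proven by blind biopsy or routine sampling

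**Formula.** Expected endpoint = [(1−u)·sc + u·su] / [(1−u) + u·su + u·(1−su)·b].

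**Example: u = 0.2, sc = 0.8, su = 0.4.** The numerator is 0.8×0.8 + 0.2×0.4 = 0.72.
- b = 0: denominator 0.8 + 0.08 = 0.88; endpoint 0.82
- b = 0.25: denominator 0.88 + 0.2×0.6×0.25 = 0.91; endpoint 0.79
- b = 1: denominator 1.00; endpoint 0.72

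Uncued detection of occult lesions is 0.40 in all three.

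**Range.** Over u of 0.1 to 0.4, sc of 0.6 to 0.9, su of 0.2 to 0.4 and b of 0 to 1, the endpoint exceeds su by 0.12 to 0.71. The smallest gap is at u = 0.4, sc = 0.6, su = 0.4, b = 1: 0.52 − 0.40. The largest is at u = 0.4, sc = 0.9, su = 0.2, b = 0: 0.62/0.68 = 0.91, less 0.20.

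**Direction.** At b = 1 the gap is (1−u)(sc − su), so its sign depends on whether known lesions are called more often than occult ones are found. If su = sc, the gap is 0.00 at b = 1. Over the same u and sc it rises to at most 0.11, at u = 0.4, su = sc = 0.6, b = 0: 0.60/0.84 = 0.71. That remainder has nothing to do with cueing. It arises because occult lesions missed by NIR and not sampled never reach the denominator.

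**Occult lesions alone.** Among proven metastases that were not clinically known, the expected percentage is su/[su + (1−su)·b]. With su = 0.4 this is 1.00 at b = 0, 0.4/0.55 = 0.73 at b = 0.25, and 0.40 at b = 1. Even this subset is informative only to the extent that NIR-negative tissue is sampled.

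**Cue alone, within evident lesions.** Suppose that, of 40 evident metastases, 24 are called on an uncued sweep and 8 more only on a directed look. The endpoint reads 32/40 = 80%, against 24/40 = 60% called on the sweep. The 20-point difference merely restates the assumption; it shows what a log would reveal, not how large the effect is.

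**The case against.** A reader might infer that the endpoint measures nothing but cued confirmation and overstates detection by a definite amount. The protocol does not support that, for four reasons.
- Malignant NIR-only spots count in the endpoint, and blind biopsies and node sampling can bring in lesions that nobody suspected.
- No text says the camera is aimed at known lesions or that clinical inspection comes first. The flow chart only places NIR imaging before resection, and finding NIR-only spots implies imaging beyond known tumour. Cueing is permitted, not prescribed.
- Additional metastases found by NIR have their own secondary endpoint. A technique that only confirmed known tumour would show few of them, and the tumour-to-background ratio would expose weak contrast.
- The direction and size of any bias rest on rates that the protocol does not give.

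It is also fair to say that a 15-patient pilot may first ask whether proven metastases fluoresce at all, and that debulking patients suit that question. The research question in section 2.2 omits the word occult, as do the primary objective and the endpoint.

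All of this narrows the point without removing it. The mixture is reported unseparated. The secondary endpoint is a count with no denominator, and it does not show whether NIR would have found the evident lesions unaided. The question in section 2.2 is confined to clinically low-stage patients, so a percentage built on debulking lesions would not answer that version either.

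**Conclusion.** The concern holds in this form: the primary endpoint does not separate metastases that NIR found independently from known metastases that fluoresced, and the protocol sets no order or separate logging that would allow the separation later. A high pooled percentage would show that proven metastases tend to fluoresce. It would not show that NIR identifies occult metastases, and it would be weak support for a detection sensitivity.

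The size of any overstatement cannot be derived from the document. Under assumed rates it runs from 0.12 to 0.71 when NIR finds 0.2 to 0.4 of occult lesions, and from 0.00 to 0.11 when known and occult lesions are called equally often. The first range mixes cueing with the difference between evident and occult lesions. That known lesions dominate in debulking patients is likely, but the protocol does not state it. Upward bias is plausible, not demonstrated.

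**What to change.** In sections 2.4 and 2.7:

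1. Start NIR imaging with a sweep of the exposed regions, and log the in vivo calls before clinically marked lesions are revisited with the camera. Record fluorescence seen only on resected tissue separately.
2. For each proven metastasis, record the route of detection (clinically known, NIR-only, or blind biopsy/routine sampling) and whether it was called on the sweep or only on a directed look.
3. Keep the fluorescence percentage, but report it by route and by stage group. Give NIR-only metastases as a count, since their percentage is 100% by construction.
4. Base any conclusion on occult disease only on proven metastases that were not clinically known, and state that unsampled NIR-negative tissue leaves this figure too high.

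These are recording and reporting rules; what is biopsied or resected does not change. The cost is one log sheet, some added imaging time, small subgroup counts and a possibly less favourable headline. The sweep does not remove all cueing: without a blinded reader, tumour visible in the open field still guides the operator. Nor does it make results in evident lesions transferable to occult ones. Both limits should be stated.
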